#### Secondary objectives

Secondary objectives include the impact of the mHealth platform use in terms of control of blood pressure and cholesterol, modification of body weight, amount of physical activity, number of hospitalisations, adherence level to prescriptions, improvements of quality of life, satisfaction and usability of the application at different follow-up times within and between groups.

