Participants in the control group are asked to record their health-related data such as body weight, BP, glycaemic levels, results of laboratory tests and diagnostic tests as usual (e.g. on a paper diary). Other information collected by the control group participants during the follow-up period can be shared, as routinely done, with their GP.

For the App functions described above and according to the Medical Device Regulation (MDR) (EU) 2017/745 requirements [2], the TreC Diabete App cannot be considered a medical device. The App does not perform operations on clinical data; it is used as data archive and for communication and simple research purposes. It does not provide direct recommendations to participants based on algorithms; it does not make changes or alterations to the collected data and it does not transfer data with implantable devices eventually belonging to the participants. Moreover, the App does not provide direct recommendation to the clinicians for diagnosis and treatment; it cannot be used to handle emergency situations.

Table 3 depicts the list of the therapeutic goals that people with T2DM should reach set by the current national and international guidelines [28–31].

**Table 3 Tab3:** List of therapeutic goals as set by the current national and international guidelines [28–31]

Type of target	Values
Glycaemic target	HbA1c < 53 mmol/mol
BP target	sBP < 130 mmHg if < 65 years old sBP < 140 mmHg if ≥ 65 years old dBP ≥ 70 mmHg and < 80 mmHg
Lipid target	LDL cholesterol < 70 mg/dl non-HDL cholesterol < 100 mg/dl (if triglycerides ≥ 200 mg/dl)

*Abbreviations*: *dBP* Diastolic blood pressure, *HDL* High-density lipoproteins, *LDL* Low-density lipoproteins, *sBP* Systolic blood pressure

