#### Secondary outcome measures

Secondary outcome measures are collected at different time point (for specific times of data collection refer to Table 4).Proportion of participants with Hb1Ac < 53 mmol/mol within the two arms;Difference in HbA1c levels between the two arms other than at 12 months;Reporting frequency and number of new hypoglycaemic episodes within the two arms;Proportion of participants reaching the targeted lipid profile (LDL level < 70 mg/dl and non-HLD cholesterol level < 100 mg/dl) and BP levels (sBP < 130 mmHg or > 140 if ≥ 65 years old);Effect on weight, lipid profile and BP levels for the App users;Effect on physical activity performed during the last 7 days prior filling in the questionnaire, for both arm participants;Number of hospitalisation events within the two arms;Number of measurements and level of physical activity with the prescribed activities (body weight monitoring, BP measurements, physical activity) within the two arms;Changes in quality of life (QoL) scores for participants of both arms;Satisfaction and usability score of the App in the intervention arm;

**Table 4 Tab4:** Time schedule of enrolment, interventions and assessments during the study period, adapted from the example template provided by the SPIRIT Group [28]

	Enrolment		Allocation		Post-allocation			Close-out	Personnel and participant involvement	Method of data collection
Timepoint	14 to 21 days prior T0	7 to 14 days prior T0	0 months	0 months (T0)	3 months (T1) (± 30 days)	6 months (T2) (± 30 days)	9 months (T3) (± 30 days)	12 months (T4) (± 30 days)		
ENROLLMENT										
** Informal study information**	x	x							Clinician	Scheduled appointment at clinic
** Eligibility screen**	x	x							Clinician or PI	Scheduled appointment at clinic
** Informed consent signed**		x							Clinician or PI and participant	Face-to-face meeting
** Allocation**			x						Research team	Face-to-face meeting
** Blood tests prescription**		x							Clinician	Face-to-face meeting
** Provide 3 copies of IPAQ questionnaire**		x							Research team	Face-to-face meeting
INTERVENTION										
** App education and instruction manual**				x					Research team	Face to face meeting
** Inform GP of participation**				x					Clinician	Through email
** Help and support with the App use**				x	x	x	x	x	Research team	Phone- email
** App (intervention) monitoring**				x	x	x	x	x	Clinician or research team	Medical dashboard

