** Medical intervention via App – data recording**				x	x	x	x	x	Clinician and participant	Medical dashboard
ASSESSMENTS: clinical and biohumoral variables and clinical indicators										
** Body weight and number of checks (previous month)**		x			x	x	x	x	Research team	Face to face meeting, medical dashboard /App or other recording tools
** Vital signs and number of checks (previous month)**		x			x	x	x	x	Research team	Face to face meeting, medical dashboard/App or other recording tools
** Demographic characteristics and clinical variables**^**a**^		x							Clinician and research team	Face to face meeting, HIS
** Hb1Ac levels and number of checks**		x			x	x	x	x	Clinician, research team, laboratory personnel	HIS
** Other blood tests**^**b**^		x						x	Clinician, research team, laboratory personnel	HIS
** Questionnaires (SF-12/MMAS-4/DASI)**				x				x	Research team, participant	Face to face meeting
** IPAQ questionnaire**				x	x	x	x	x	Research team, participant	Face to face meeting and phone call
** SUS questionnaire (App group only)**								x	Research team, participant	Face-to-face meeting
** Number of nursing and medical (tele)consultation and chat interactions**					x	x	x	x	Research team	Medical dashboard/App and HIS
** Number of unscheduled specialists visits (macro- and micro-vascular complications), number of accesses to ED for cardiac, cardiovascular or diabetic problems**					x	x	x	x	Research team	HIS
** Number of therapeutic plan changes**					x	x	x	x	Research team	Medical dashboard/App and HIS
** Time spent for (tele)consultation**						x			Research team	Recording of time during visit
** Number of hospitalisation**						x	x	x	Research team	HIS
** Number of hypoglycaemic episodes**					x	x	x	x	Research team, participants	Medical dashboard/App and/or download of data from glucometer

*Abbreviations*: *DASI* Duke Activity Status Index, *ED* emergency department, *HbA1c* Glycosylated Haemoglobin Type A1C, *HIS* Hospital Information System, *IPAQ* International Physical Activity Questionnaire, *MMSA-4* Morisky Medication Adherence Scale, *SF-12* Short Form-12, *SUS* System Usability Scale, *PI* Principal Investigator

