## Data collection and management

### Plans for assessment and collection of outcomes {18a}

The large majority of the data (e.g. demographic data, clinical information) are collected as part of the standard routine practice. Other data are collected through interviews and questionnaires that are provided during different times of the study. Those assigned to the intervention group will be asked to provide information through the App (e-diary and Virtual Coach), whilst those assigned to the control group will register the data as per routine (e.g. paper diary). Please refer to Table 4 under the “Outcomes {12}” section for the information regarding the involvement of personnel—participants and the source of information used for data collection.

Below, a short description of the questionnaires used during this study is provided:Quality of life questionnaire “SF-12”: composed of 12 items (obtained from 36 items of the original SF-36 questionnaire) and providing two measures related to two different aspects of health: physical health and mental health [33, 34].Activity status evaluated through the “Duke Activity Status Index—DASI scale”, which measures the functional capacity perceived by the participant. It is a 12-item scale with a score that ranges from 0 (worst) to 58.2 (best). A difference of 2 or more is considered clinically significant [35, 36].Daily physical activity level, evaluated using the “Physical Activity Questionnaire Daily – IPAQ” questionnaire, composed of 4 generic items with open-ended questions regarding last 7-day recall of physical activity [37];Evaluation of medication adherence using the Morisky Medication Adherence Scale in the 4-item version (MMAS-4) [38]. The scale consists of 4 questions with a score of 0 and 1 for a “Yes” and “No” answer, respectively. The questions are summed to give a range of scores from 0 (high adherence) to 4 (low adherence). The questionnaire answers will be collected during the face-to-face meeting with the research team.App user satisfaction using the System Usability Scale (SUS): The scale consists of 10 questions with a score ranging from 1 (strong disagreement) to 5 (strong agreement). Each score is then multiplied by 2.5, resulting in a total score ranging from 0 to 100. A 68 score is considered above average [39].

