### Adverse event reporting and harms {22}

Due to the nature of the intervention, no harm is expected. However, cyber security for both medical dashboard and the App needs to be guaranteed in order to protect personal data of the participants involved in the study. Healthcare staff members will receive appropriate training in the use of the technological platform. A username and a password will be provided to each healthcare staff member involved in the study, who will then be able to access the platform only by entering their username and personal password. A help desk is available to help and support the participant as well as the healthcare staff involved in the project. Efforts have been put in place and will be put in place to protect personal data in compliance with the EU GDPR 2016/679 and the subsequent national Italian laws, including the Data Protection Code (D.lgs. 196/2003) [21, 22]. The data controller and processor has implemented technical and organisational measures to safeguard data protection principles (Art. 5 GDPR) and guarantee the rights to the data subjects (Artt. 15–21 GDPR). Data collected will be pseudo-anonymised and pooled before being shared with third parties, as specified in the privacy policy that participants have to access and sign upon the start of the study. The data processor has been designated through a specific contract under Art. 28 of the GDPR and the data protection officer of both the data controller and processor will support the compliance with the legal requirements. Episodes of hospitalisation or complications due to T2DM itself (e.g. hypoglycaemic episode) will not be considered as an adverse event of the trial intervention or trial conduct.

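### Two secondary outcomes, the hypoglycaemia count and the weight, lipid and BP effect, are not like-for-like randomised comparisons as written

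*Protocol article*

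**What the plan says.** **Hypoglycaemia.** The list under Secondary outcome measures asks, for both arms, how often episodes are reported and how many new ones occur. Table 4 gives the source at 3, 6, 9 and 12 months: "Medical dashboard/App and/or download of data from glucometer". The App is prescribed to the intervention arm only. For the other arm, Intervention description {11a} says: "Participants in the control group are asked to record their health-related data such as body weight, BP, glycaemic levels" and test results in their usual way, a paper diary being the example. Section {18a} repeats this split. Section {11c} gives App reminders to the intervention arm, with measuring and recording blood sugar as the example. Section {17a} states that the person collecting data cannot be blinded. Section {22} says that diabetes complications, hypoglycaemia included, "will not be considered as an adverse event of the trial intervention or trial conduct".

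**Weight, lipids and BP.** One listed outcome is "Effect on weight, lipid profile and BP levels for the App users". The secondary objectives name BP, cholesterol and body weight among measures to be assessed "at different follow-up times within and between groups". Section {20a} applies intention-to-treat and per-protocol analysis to secondary endpoints. In Table 4 only the SUS questionnaire is marked as being for the App group. Body weight comes from "Face to face meeting, medical dashboard /App or other recording tools", and vital signs have the same three options. Lipids come from the hospital information system at baseline and 12 months.

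**The concern.** A randomised comparison of event counts needs the same chance of detecting an event in each arm. Here one arm has an additional, prompted recording channel, and the choice of source is left open. Fuller recording in the App arm would look like more hypoglycaemia, or would hide a true reduction. The opposite is also possible: if intervention counts rest on manual App entries alone while control counts come from meter downloads, the App arm could be under-counted. The plan has no way to separate these effects from a real difference. Because episodes are not handled as adverse events, this outcome is the trial's only hypoglycaemia-specific count.

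A change in weight, lipids or BP among App users alone does not show what the platform does. Section {6b} gives both arms the same care pathway, so some change is to be expected without the App. Only the contrast with the control arm isolates its contribution.

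**Working it through.** **Step 1. The plan's own figures.** The article gives no expected hypoglycaemia rate or capture rate. The only usable size is the sample size under {14}, which reproduces: n = (3² + 7²)(1.960 + 0.842)² / (52 − 49)² = 50.58, so 51 per group and 102 in total.

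**Step 2. Sources by arm.**

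| Measure | Intervention arm | Control arm | Same source guaranteed? |
|---|---|---|---|
| Hypoglycaemia | App/dashboard and/or glucometer | glucometer only, among those listed; the paper diary is not listed in this row | No |
| Weight, BP | face-to-face, App or other tools | face-to-face or other tools | No, but possible |
| Lipids, HbA1c | hospital information system | hospital information system | Yes |

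**Step 3. Illustration for hypoglycaemia.** Assumptions, none from the documents: equal true rates, Poisson episodes, and capture proportions c1 (App arm) and c0 (control). The 51 per arm is the plan's.

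- Apparent rate ratio = c1/c0: 0.9/0.7 = 1.29; 0.9/0.5 = 1.80.
- With λ true episodes per person, SE of the log ratio = √[1/(51λc1) + 1/(51λc0)], and Z = ln(c1/c0)/SE.
- Probability of p < 0.05 with no true difference = Φ(Z − 1.96) + Φ(−Z − 1.96).

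| Capture, App vs control | Ratio | λ = 1 | λ = 2 | λ = 4 |
|---|---|---|---|---|
| 90% vs 90% | 1.00 | 0.050 | 0.050 | 0.050 |
| 90% vs 70% | 1.29 | 0.203 | 0.357 | 0.615 |
| 90% vs 50% | 1.80 | 0.663 | 0.920 | 0.997 |

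Worked line for 90% vs 70%, λ = 1: SE = √(1/45.9 + 1/35.7) = 0.223; Z = 0.251/0.223 = 1.13; probability = 0.203.

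A milder gap of 72% against 60% gives 0.72/0.60 = 1.2. Reversed capture, 70% in the App arm against 90% in controls, gives 0.7/0.9 = 0.78. Conversely, a true ratio of 0.78 combined with a capture ratio of 1.29 appears as 1.00, so a real benefit could vanish. The ratios do not depend on the Poisson assumption. The probabilities do, and over-dispersed counts analysed appropriately would give smaller ones.

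**Step 4. The App-user outcome.** Other items in the outcome list say whether they cover both arms or the intervention arm. This one names App users. That conflicts with the secondary objectives, which include between-group assessment of the same measures, and with the two-group analysis by intention to treat in {20a}. No arithmetic applies.

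**The case against.** Several counter-arguments stand and limit the point.

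- **Weight and BP.** A reader might infer that these are captured by App in one arm and by usual recording in the other. Table 4 does not say so: a face-to-face meeting is listed first, without restriction by arm, and other questionnaires at 12 months are completed face to face. What remains is that the source is not fixed. The 12-month appointment may be remote ({6b}), and standardised nurse measurement is stated only before randomisation ({17a}), so the source may differ by arm.
- **Lipids.** These are laboratory values in both arms. Only the wording of the outcome is at fault.
- **App users.** This may simply mean the intervention arm. No usage threshold is given, so a usage-selected analysis cannot be inferred. The separate outcome on reaching lipid and BP targets is not limited to App users, and a within-group analysis is legitimately among the objectives.
- **Safety.** It is tempting to call this the trial's only safety signal. Emergency accesses for diabetic problems and hospitalisations are collected from the hospital system without restriction by arm and may catch severe episodes, though neither is specific to hypoglycaemia.
- **Recording is partly measured.** Reporting frequency is an outcome. However, the numbers of checks in Table 4 concern weight, vital signs and HbA1c, not glucose self-tests.
- **A common glucometer source is no full cure.** Prompted participants may test more often and so detect more low values. This is correct, and the fix has to allow for it.

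The full protocol may settle more detail. But the article itself states the open source and the App-user wording, so these are not mere omissions.

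**Conclusion.** The point holds for two secondary outcomes. The hypoglycaemia count depends on recording channels that differ by arm, and the weight, lipid and BP effect is worded as a within-arm contrast at odds with the article's own objectives and analysis population. For weight and BP there is a lesser point, that the measurement source may differ by arm.

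The size of any hypoglycaemia bias is unknown. Apparent ratios of 1.29 to 1.80, with false-positive probabilities from about 20% to over 99%, show what assumed capture gaps of 20 to 40 percentage points would do. They are not estimates for this trial, and the direction is not certain.

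A reader might infer that the trial's main result is compromised. The documents do not support that: HbA1c is processed in the laboratory and taken from the hospital information system in both arms. The correction is worth making but does not touch the primary analysis.

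**What to change.** 1. **Hypoglycaemia.** In Table 4 and the outcome list, base the between-arm count on the same source in both arms: glucometer download where available. Report episodes known only from the App descriptively. Report the number of glucose tests per arm, or episodes per test, because prompted testing can still raise detection. State how many participants in each arm have a download.
2. **Weight, lipids and BP.** Replace the App-user wording with the baseline-adjusted between-arm difference at 12 months in all randomised participants. Label any change within the App arm as descriptive. Section {20a} names only two-group tests such as the t test, so a linear model with the baseline value as covariate would have to be added.
3. **Source of weight and BP.** Use the face-to-face measurement for the 12-month comparison in both arms where it is available.

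**Cost.** Mostly wording, since these sources are already listed. Episodes entered only in the App, and symptomatic episodes without a test, leave the comparative count. Participants without a download are missing from it; the article does not say that everyone has a downloadable meter. Participants seen only remotely at 12 months lack a face-to-face weight or BP and would fall under the missing-data approach in {20c}.

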#### Process indicators

To assess the organisational implications of this novel approach the following process indicators will be collected:Number of telemedicine visits between participants and nurses and chat interactionsNumber of telemedicine visits between participants and clinicians and chat interactionsNumber of (tele)specialist consultations (e.g. cardiology visit)Number of changes in the therapeutic plan (e.g. drug prescription and dosage)Amount of time spent for telemedicine visits (calculated on the basis of the average time spent to deliver eight consecutive nursing visits and eight consecutive medical visits, as delivered at 6 months).

### Participant timeline {13}

Participants will be followed for 12 months (± 30 days)—T4—starting from the allocation time (T0). Post-allocation evaluations are set to be at 3, 6 and 9 months (± 30 days)—(T1, T2 and T3, respectively). Table 4 depicts the time schedules of enrolment, interventions and assessments at different time points [32].

### Sample size {14}

The sample size was calculated on the basis of the primary hypothesis (Hb1Ac levels are likely to decrease more in the subjects of the intervention group than for the subjects of the control group at 12 months). A lower variability around the HbA1c mean level is also expected for the subjects in the intervention group when compared to the HbA1c mean level for the subjects in the control group. It was assumed that at 12 months, the mean Hb1Ac level will be 49 (SD ± 3) mmol/mol in the intervention group and 52 (SD ± 7) mmol/mol in the control group. In order to achieve a power of 80% and to keep the significance level at 5%, the sample size was calculated to be 102 (51 in each group) by using Open Epi (a freely accessible software, https://www.openepi.com/Menu/OE_Menu.htm) as depicted in Fig. 1 below. Assuming 20% of drop-out, the required sample was calculated as 120.

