### Eligibility criteria {10}

Participants must meet at randomisation all the inclusion criteria and none of the exclusion criteria listed in Table 1.

**Table 1 Tab1:** Inclusion and exclusion criteria

Inclusion criteria	Exclusion criteria
• Being diagnosed with T2DM; • Aged ≥ 18 and ≤ 85 years old; • Having an HbA1c level > 7% (53 mmol/mol) and < 12% (108 mmol/mol); • Being able to walk without walking aids; • Having provided written informed consent; • Having a smartphone or a tablet and being able to download the App that will be used to insert the required data	• Having a BMI < 18 kg/m^2^ and > 45 kg/m^2^; • Having a sBP < 100 or > 200 mmHg and/or dBP < 50 or > 120 mmHg; • Being diagnosed with a stage 5 CKD^a^ • Being diagnosed with a NYHA stage IV; • Poor collaboration (i.e. unwilling to modify the actual plan of control and therapy, even if not ideal) for which adherence to the study is unlikely • Having no possibility of using a smartphone or a tablet • Having medical conditions affecting the study participation (i.e. life expectancy < 1 year)

*Abbreviations*: *BMI* body mass index, *CKD* chronic kidney disease, *dBP* diastolic BP, *HbA1c* glycated haemoglobin type A1c, *NYHA* New York Heart Association, *T2DM* type 2 diabetes mellitus, *sBP* systolic BP

^a^based on the glomerular filtration rate according to the CKD-Epidemiology Collaboration equation < 15 ml/min/m^2^ accounting for individual body surface [20]

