## Statistical methods

### Analysis primary and secondary endpoints {20a}

The analyses of the primary and secondary endpoints will be performed based on the intention-to-treat and as per-protocol approaches. Continuous variables of the two groups will be presented as mean, SD and quartiles, whilst categorical variables will be presented as percentages.

The normality of the distributions is determined by using the normality test of Kolmogorov–Smirnov. To compare the differences between the two groups for continuous outcomes, Student’s *T* test will be used. If the assumption of normality of data distribution does not hold, Wilcoxon’s rank sum test will be used. For repeated measures of continuous variables for which there is an assumption of normality of data distribution, the one-way ANOVA test will be used. If the assumption of normality does not hold, the Friedman test will be used instead of the one-way ANOVA test.

Chi-squared test will be used for categorical outcomes. SAS 9.4 (SAS Institute Inc.) will be used to conduct analyses. For all tests, the significance level is set to 0.05 (2-sided). Professional statisticians ([name]) will conduct all analyses.

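### The stated 80% power for 3 mmol/mol rests on a weakly supported App-arm SD of 3; with the protocol's own control SD of 7 in both arms it is about 55% to 64%

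*Protocol article*

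**What the plan says.** The Sample size section of the protocol article assumes 12-month HbA1c values of "49 (SD ± 3) mmol/mol in the intervention group and 52 (SD ± 7) mmol/mol in the control group". The only reason it gives for the much smaller App-arm SD is that less variability is expected there. At 80% power and a 5% level, "the sample size was calculated to be 102 (51 in each group"); the section then adds "Assuming 20% of drop-out, the required sample was calculated as 120". The statistical methods section confirms that "the significance level is set to 0.05 (2-sided").

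Three other places bear on these values:

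- **Eligibility criteria {10}, Table 1.** The entry criterion, which applies at randomisation, is "Having an HbA1c level > 7% (53 mmol/mol) and < 12% (108 mmol/mol"). The abstract describes the target population as poorly controlled.
- **Intervention description {11a}, Table 3.** The glycaemic goal is "HbA1c < 53 mmol/mol", the same value as the entry floor.
- **Analysis primary and secondary endpoints {20a}.** The comparison of continuous outcomes is an unadjusted t test, or a rank sum test if normality fails. Baseline HbA1c does not enter the comparison, although Table 4 schedules its collection before allocation.

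**The concern.** Everyone enters above 53 mmol/mol, within a permitted window 55 mmol/mol wide. The calculation has the average control participant, on the usual care pathway, finish at 52. That is below the entry floor and inside the treatment goal. It also has the App arm finish so tightly grouped that about 95% of its members lie between 43 and 55. Both assumptions are favourable, and the SD of 3 directly lowers the required sample size.

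If the App arm is as variable as the control arm is assumed to be, the trial has much less than 80% power for the difference it was sized on. The effect estimate would not be biased. But the published power figure would mislead anyone using it to judge what a non-significant result means.

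**Working it through.** **Inputs.** From Sample size {14}: means 49 and 52 (difference 3), SDs 3 and 7, power 80%, 51 per arm, 120 randomised, 20% drop-out. From the statistical methods: two-sided 0.05. From Table 1: entry above 53 and below 108 mmol/mol. The normal quantiles give (1.960 + 0.842)² = 7.849.

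**1. The protocol's own figure.** n per arm = (SD₁² + SD₂²) × 7.849 / difference² = (9 + 49) × 7.849 / 9 = 50.58, so 51 per arm and 102 in total. Power at 51 per arm is 80.3% by the normal approximation and 79.2% by a Welch t calculation. The stated figure reproduces.

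**2. What the inputs imply, if values are roughly normal.**

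- Control arm below 53: Φ((53 − 52)/7) = Φ(0.14) = 0.557, about 56%.
- App arm below 53: Φ((53 − 49)/3) = Φ(1.33) = 0.909, about 91%.
- Central 95% of the App arm: 49 ± 1.96 × 3 = 43.1 to 54.9.
- Central 95% of the control arm: 52 ± 1.96 × 7 = 38.3 to 65.7.

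**3. The protocol's control SD of 7 in both arms, difference still 3.** n per arm = (49 + 49) × 7.849 / 9 = 85.5, so 86. Power is taken from the noncentral t distribution with 2n − 2 degrees of freedom and noncentrality 3 / (7 × √(2/n)). The detectable difference is 2.802 × 7 × √(2/n).

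| Analysed per arm | Where it comes from | Noncentrality | Power | Difference detectable with 80% power |
|---|---|---|---|---|
| 48 | 120 × 0.8 / 2 | 2.10 | 55% | 4.0 mmol/mol |
| 51 | stated target | 2.16 | 57% | 3.9 mmol/mol |
| 60 | no loss from 120 | 2.35 | 64% | 3.6 mmol/mol |

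The normal approximation gives 56% and 58% in the first two rows. An intermediate case, SD 5 in the App arm and 7 in control, needs 65 per arm and has about 70% power at 51 (normal approximation).

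**4. Is the loss due to drop-out?** Hardly. On the protocol's own SDs, 48 per arm still gives 77.9% (normal approximation).

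**5. Larger SDs, as sensitivity only.** The document gives no such values; a common SD of 10 or 12 is an assumption.

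| Assumed common SD | Needed per arm | Power at 48 per arm | Detectable difference at 48 per arm |
|---|---|---|---|
| 10 | 175 | 31% | 5.7 mmol/mol |
| 12 | 252 | 23% | 6.9 mmol/mol |

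**6. Baseline adjustment.** With baseline-to-12-month correlation r, the residual SD is SD × √(1 − r²). For an assumed r = 0.7 at 48 per arm, SD 7 becomes 7 × √0.51 = 5.00 and power is about 83%. SD 10 becomes 7.14 and power is about 53%. The planned unadjusted test obtains none of this gain.

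**7. Width of the unadjusted 95% confidence interval at 48 per arm.** Half-width = 1.986 × SD × √(2/48): 2.84 mmol/mol at SD 7 and 4.05 at SD 10.

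**The case against.** The strongest reply is that nothing here is contradictory. The entry limits apply at randomisation and the planning values at 12 months. Both arms receive guideline care aimed at a value below 53, and selecting people above a cut-off invites regression to the mean. That stands. A reader might infer that the eligibility criteria rule out 49 and 52; they do not. What remains is a judgement that four favourable values are thinly supported for this population.

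A reader might also take the wide entry window to show that the true SD is 10 or more, so that real power is 23% to 31%. The document does not support this. A permitted range is not a distribution, and enrolled values may cluster just above 53. Only the SD 7 result uses the protocol's own number.

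Nor is the 80% mostly a product of the SD of 3. That arm contributes 9 of the summed variance of 58, about 16%. Replacing 3 by 7 takes power from 80% to 57% at 51 per arm, a substantial loss but not a collapse.

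Finally, a reader might conclude that a null result would say nothing about 3 mmol/mol. At SD 7 the half-width of about 2.8 means that an estimate close to zero would exclude 3.

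Two further points favour the sponsor. Hospital-record access may recover outcomes for non-completers, which is why 60 per arm is shown. The 56% and 91% depend on approximate normality.

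**Conclusion.** The point holds as a weakness in the planning inputs, not as an arithmetic error or an inconsistency. The stated 80% power depends on an App-arm SD of 3 for which the article offers only an expectation. It is paired with means that require the average participant in both arms to finish below the entry floor.

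With the protocol's control SD of 7 in both arms, power for 3 mmol/mol is about 55% to 64%, depending on how many of the 120 are analysed. At 48 per arm the chance of missing a true 3 mmol/mol difference is then about 45%.

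This rests on three assumptions: the App arm is no less variable than the control arm, the SD of 7 is itself right, and the test is the planned unadjusted t test. The actual 12-month SD cannot be settled from the document, so any larger loss of power is conditional on an assumed SD.

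**What to change.** No further enrolment is proposed.

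1. **Sample size {14}.** Restate the power and the difference detectable with 80% power for 120 randomised. Use SD 7 in both arms as the base case, over the 48 to 60 per arm that may be analysed. Show a range of larger SDs labelled as assumptions. If there is evidence for the SD of 3, give it here.
2. **Analysis primary and secondary endpoints {20a}.** Name a comparison of 12-month HbA1c adjusted for baseline HbA1c (ANCOVA) as the primary analysis, before outcomes are compared by arm. Baseline values are already collected. Credit the power gain only once this is in place, with the assumed correlation stated.
3. **Interpretation.** Say that a non-significant result will be read from its 95% confidence interval. Do not state in advance that such a result cannot exclude 3 mmol/mol, because at SD 7 it may.

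The cost is a less favourable stated power and a slightly longer analysis section. No new data, visits or participants are needed.

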### Methods in analysis to handle protocol non-adherence and any statistical methods to handle missing data {20c}

The analysis will be conducted by “intention to treat” and “per protocol”. Given our expectation that very few patients will crossover or be lost to follow-up, these analyses should agree very closely.

Missing data will be managed according to the SAS version 9.3 MI procedure, which consists of the multiple imputation methods chosen by pattern of data missingness and type of imputed variable (SAS Institute Inc.)

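### The randomised total of 120 does not follow from 102 evaluable participants with 20% drop-out: it covers 15%, and at 20% the power is about 78% (a minor correction)

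*Protocol article*

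**What the plan says.** All planning figures stand in one paragraph of the protocol article, Sample size {14}. At 12 months it assumes that "the mean Hb1Ac level will be 49 (SD ± 3) mmol/mol in the intervention group" and "52 (SD ± 7) mmol/mol in the control group". For 80% power at the 5% level it reports that "the sample size was calculated to be 102 (51 in each group"), using Open Epi. It then adds: "Assuming 20% of drop-out, the required sample was calculated as 120".

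Four other sections bear on the point:

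- Analysis primary and secondary endpoints {20a} makes all tests two-sided at 0.05.
- Trial design {8} sets 1:1 allocation.
- Recruitment {15} ends recruitment once the target size is reached.
- The section on non-adherence and missing data {20c} plans multiple imputation. On the intention-to-treat and per-protocol analyses it says: "Given our expectation that very few patients will crossover or be lost to follow-up, these analyses should agree very closely".

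**The concern.** An allowance for drop-out should leave the required evaluable number after the stated fraction has been lost. Here the required number (102), the fraction (20%) and the result (120) are all given, and they do not fit together. This is not an omission that a fuller document might fill.

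At stake is the power claim for the primary endpoint. Because recruitment stops at the target, a target set too low is not made up later. If 20% do drop out without an outcome, the trial falls short of its stated 80% under its own assumptions, and a reader would take the design to tolerate more attrition than it does.

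**Working it through.** **Inputs.** From Sample size {14}: difference 52 − 49 = 3 mmol/mol; SDs 3 and 7, so the variances sum to 9 + 49 = 58; power 80% (z = 0.8416); drop-out 20%. From the analysis section {20a}: two-sided 5% (z = 1.96). From Trial design {8}: 1:1 allocation.

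**Step 1: reproduce the 102.** By the normal approximation for two means with unequal SDs:

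n per arm = (1.96 + 0.8416)² × 58 / 3² = 50.58, rounded up to 51, so 102 in total.

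This matches the plan. A one-sided 5% level would give 39.84, so 40 per arm, and does not match. The method and the sidedness are therefore not in doubt.

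**Step 2: allow for 20% drop-out.**

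- Correct inflation: 102 / (1 − 0.20) = 127.5, so 128 (64 per arm).
- The common shortcut: 102 × 1.2 = 122.4. This is wrong in principle and is not 120 either, though 120 may be that figure rounded down.
- Drop-out that 120 does cover: 1 − 102/120 = 0.15, or 15%.
- Gap to the correct figure: 128 − 120 = 8 participants.

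**Step 3: what 120 delivers.** 120 × 0.80 = 96, or 48 per arm with equal losses.

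**Step 4: power by the same method as Step 1.** Power = Φ(3/√(58/n) − 1.96).

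- n = 51: Φ(2.813 − 1.96) = 80.3%.
- n = 48: Φ(2.729 − 1.96) = 77.9%.

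| Drop-out from 120 | Evaluable | Per arm | Power |
|---|---|---|---|
| 10% | 108 | 54 | 82.5% |
| 15% | 102 | 51 | 80.3% |
| 20% | 96 | 48 | 77.9% |

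**Step 5: does the choice of method matter?** Going from 51 to 48 per arm, power falls from 79.6% to 77.1% by the pooled t test and from 79.2% to 76.7% by the unequal-variance t test. The loss is about 2.5 points by either, close to the 2.4 points of Step 4.

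**The case against.** The arithmetic cannot be defended, but its weight can be disputed, and most of that dispute stands.

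- **The effect is small.** A loss of 2.4 points is less than ordinary uncertainty about the SDs would cause. With a control SD of 7.25 instead of 7, the variances sum to 9 + 52.56 = 61.56, and power at 51 per arm is Φ(3/√(61.56/51) − 1.96) = 78.0%, about the same fall. This stands.
- **A drop-out need not be a lost outcome.** A reader might infer that the error fixes the final information at 96 participants. The documents do not support that. The retention section {18b} provides for collecting clinical outcomes from the hospital information system for people who do not complete. HbA1c results are registered there automatically, Table 4 schedules HbA1c at 3, 6, 9 and 12 months, and multiple imputation is planned. So 96 counts completers, not necessarily participants with usable data. The sample-size paragraph takes no credit for any of this, however, so it does not make 120 right.
- **Few losses are expected.** A reader might infer that section {20c} contradicts the 20%. It gives no rate, and planning for more attrition than one expects is ordinary caution. The two statements are in tension, not in contradiction. If losses stay at or below 15%, 120 is enough on the plan's own method.
- **A larger shortfall can be made to appear.** Setting the unequal-variance figure of 76.7% against the stated 80% suggests a gap of 3.3 points. By that same method the plan's own 51 per arm gives 79.2%, so part of the gap comes from changing the method.

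One could also suppose that 120 was chosen to suit the blocks of 10. The article does not say so, and rounding down would still leave too few completers.

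**Conclusion.** The point holds as a minor correction. The required total is wrong as stated: 20% drop-out calls for 128, and 120 allows for 15%. If 20% are lost evenly from both arms and none of their outcomes are recovered, power is 77.9% instead of 80.3%, given the plan's difference of 3 mmol/mol, SDs of 3 and 7, and a two-sided 5% test. Recovered or imputed outcomes would narrow that gap by an amount the article does not allow one to calculate. Nothing here biases the comparison of the arms or makes the trial uninformative.

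**What to change.** In Sample size {14}, replace the drop-out sentence with: *120 randomised gives 80% power with up to 15% drop-out; with 20% drop-out 96 are evaluable and power is about 78%.* This costs wording only. It needs no further participants, and the power claim becomes slightly less favourable but true.

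As a remark, word the expectation about losses in section {20c} to agree with the attrition allowance, for instance by saying that the allowance is a cautious upper figure and not the expected rate.

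Raising the target to 128 is not proposed. It would change the recruitment target, and the article, published in August 2023, gives April 2023 as the planned end of recruitment. Eight more participants may not be obtainable, and the gain would be small.
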